#### ② Inclusion/exclusion criteria

Subjects should be reviewed by the investigator or their delegate to ensure that the subject is suitable for the study.

#### ③ Demographic information and risk factor/medical history surveys

Demographic information surveys of the clinical trial subjects are conducted. Recorded items include subject sex, age, risk factors, medical history related to cardiovascular disease, clinical diagnosis, and other past medical history.

#### ④ Physical measurements and vital signs

Height and weight are measured. Vital signs including blood pressure, and heart rate are measured before any other planned tests are conducted.

## ⑤ Clinical laboratory test

|                   |                                                                      |
|-------------------|----------------------------------------------------------------------|
| CBC               | Hemoglobin, WBC, Platelets                                           |
| Chemistry profile | Creatinine, Fasting glucose level, AST,ALT, T-bilirubin, LDH, Sodium |
| Perfusion         | Lactate, ScVO2                                                       |
| Cardiac enzymes   | CPK, CK-MB, Troponin I, NT-proBNP                                    |

## ⑥ Medication history

The medication history is investigated through interviews and past medical records.

## ⑦ Survival and death event investigation

## ⑧ Echocardiography

## ⑨ Coronary angiography for ischemic heart disease

## ⑩ Insertion of left ventricular assist device and investigation of complications

**12.2. Follow-up**

Visits are conducted at 1 month, 6 months, and 12 months after the shock event for the following tests and procedures. Information gathering through phone (landline contact) is also allowed without the subject's visit.

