Recently, in a study conducted by Thiele et al., the superiority of IABP treatment was not demonstrated compared to standard treatment group in patients with cardiogenic shock accompanied by acute myocardial infarction for whom early coronary intervention was scheduled [2]. As a result, research on the effectiveness and safety of mechanical circulatory support devices that can more effectively assist left ventricular function in cardiogenic shock is being actively pursued worldwide [3-6]. In particular, the expected benefits of ECMO, a left ventricular assist device that can be operated anywhere in emergency situations, are significant, and interest in ECMO procedures is rapidly increasing in Korea, with the number of procedures increasing rapidly. Therefore, it is urgent to evaluate the appropriateness and effectiveness of ECMO and conduct research on its effects.

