## **11. Clinical trial method**

### **11.1. Overview**

Shock patients with cardiogenic shock caused by acute myocardial infarction, myocardial disease, myocarditis, etc. will be registered both retrospectively and prospectively for two and a half years before and after IRB approval. Patients undergoing coronary intervention and treatment are performed according to the standard method recommended by the Korean Society of Cardiology. If the patient satisfies the above conditions and meets other inclusion and exclusion criteria, we obtain the patient's consent and enroll them in the study. On the day of shock occurrence, we perform physical measurements, blood tests, investigate the medication being taken, and record the most severe signs of vitality on that day. The maximum dose of medication used for shock treatment, the insertion of a left ventricular assist device, and indicators of shock deterioration and improvement are followed up. We conduct tests scheduled for the day of shock occurrence and one month, six months, and twelve months afterward to confirm whether a death event occurred. If the subject is unable to visit the hospital due to unavoidable circumstances, the trial responsible person or the person delegated by the trial responsible person may follow-up and check the subject's survival status and death event by phone.

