## 12. Observation items/clinical examination items and observation/testing methods

### 12.1. Visit 1 (day of shock occurrence)

#### ① Written informed consent for patients enrolled

According to the scope of data collection, it is divided into prospective data collection subjects and retrospective data collection subjects.

- Prospective data collection subjects: The day of shock occurrence is after the IRB approval date
- Retrospective data collection subjects: The day of shock occurrence is before the IRB approval date

For prospective data collection subjects, before entering the clinical trial, the purpose and content of the trial should be explained in detail to the subject or legal guardian (in the case of a subject who cannot provide consent for the trial), and the written consent form should accurately record the signature dates of the subject and investigator. The original signed consent form is kept by the subject, and a copy is provided to the subject. If the subject is unable to consent on the day of the shock occurrence, the consent form is obtained from the representative of the accompanying subject. In this case, the principal investigator and sub-investigator must inform the subject or the subject's representative about the clinical trial as soon as possible and obtain consent to continue participating in the trial. If the subject recovers to a condition where consent can be given, the consent form is obtained from the subject.

For retrospective data collection subjects, only data corresponding to the study protocol are collected until IRB approval is obtained without written consent. However, among shock occurrence subjects before IRB approval, those who have obtained written consent are eligible for both prospective and retrospective data collection.

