### **15.3. Statistical analysis**

We aim to identify predictors of in-hospital death in patients who experience shock using binary logistic regression analysis. This type of analysis requires 10-15 events per independent variable, and with an expected mortality rate of about 40%, or approximately 400 deaths, we have sufficient events to study various risk factors. The goodness-of-fit of the model will be assessed using the C-statistic and Hosmer-Lemeshow test. In addition, we plan to compare the in-hospital death rate between patients with and without left ventricular assist devices using chi-square tests among those who receive a certain level of vasoactive drugs. We also aim to identify predictors of successful removal of the ECMO device and procedure-related complications such as bleeding, thrombosis, and limb ischemia using binary logistic regression analysis in patients who undergo ECMO. Finally, we plan to evaluate overall death over five years using Cox survival

analysis. We will assess the goodness-of-fit of the model by checking Schoenfeld's residuals and identify the hazard of each risk factor.

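### Study contacts due before IRB approval could not happen, so death and events after discharge are ascertained differently by cohort, and the Cox analysis of overall death has no cohort term

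*Protocol*

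**What the plan says.** - **Follow-up schedule (Protocol 12.2).** "Visits are conducted at 1 month, 6 months, and 12 months after the shock event for the following tests and procedures". A telephone call may replace the visit: "Information gathering through phone (landline contact) is also allowed without the subject's visit". Section 11.1 likewise gives confirmation of death as the purpose of these contacts. Neither section separates the cohorts or names another source of vital status, such as a death register.
- **Who is retrospective (Protocol 12.1, written informed consent).** "Retrospective data collection subjects: The day of shock occurrence is before the IRB approval date".
- **What may be collected from them (same section).** "For retrospective data collection subjects, only data corresponding to the study protocol are collected until IRB approval is obtained without written consent". The next sentence makes an exception: pre-approval subjects who gave written consent qualify for both kinds of data collection.
- **Length of the two phases (Protocol 11.1).** Patients are "registered both retrospectively and prospectively for two and a half years before and after IRB approval".
- **Analysis (Protocol 15.3).** "Finally, we plan to evaluate overall death over five years using Cox survival" analysis, with a check of Schoenfeld residuals. No cohort factor, stratum or censoring rule is given. The composite is secondary endpoint 3 in section 15.2, and no Cox model is assigned to it.

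**The concern.** Sections 12.1 and 12.2 cannot both hold for a retrospective subject without consent. The schedule applies to everyone, but a study contact cannot have been made before approval, and the data of such a subject end at approval. What is known after discharge then depends on what the enrolling hospital's records happen to show. A death, infarction, stroke or readmission elsewhere can be missed. Prospective subjects are actively sought at three fixed times.

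The endpoints exposed are death during follow-up, the composite, and 28-day death in patients discharged before day 28. If fewer late deaths are seen in the retrospective cohort, any factor whose frequency changed over calendar time can pick up a spurious association in an unstratified model. Device use is a candidate, because section 6.2 says that "interest in ECMO procedures is rapidly increasing in Korea, with the number of procedures increasing rapidly" and section 6.1 makes the treatment effects of IABP and ECMO an aim of the study.

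**Working it through.** The plan gives no figure for follow-up ascertainment to reproduce. Its power statement in section 9.3 concerns two proportions, and this point does not rest on it. The one plan figure used below is the expected 40% mortality in section 15.3: 0.40 × 1,000 = 400 in-hospital deaths, as stated there.

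**1. Which contacts were possible.** Input from section 11.1: 2.5 years = 30 months before approval. Assumption: even accrual. A contact due at month m falls after approval only if shock occurred in the last m months before it, a share of m/30.
- 1 month: 1/30 = 3% after approval, 97% before
- 6 months: 6/30 = 20% after, 80% before
- 12 months: 12/30 = 40% after, 60% before

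For prospective subjects all three fall after approval.

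**2. First-year time before approval.** With u the months from shock to approval, the mean of min(u, 12) is (12²/2 + 12 × 18)/30 = (72 + 216)/30 = 9.6 months, or 80% of the first year. With two equal cohorts this is 40% of pooled first-year time. Deaths are ignored.

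**3. Effect on the cohort contrast.** Assumptions: true 12-month post-discharge mortality m of 10-20% in both cohorts, and capture c of 70-95% of those deaths in retrospective subjects. The apparent retrospective-to-prospective hazard ratio is log(1 − mc)/log(1 − m).
- m = 0.20, c = 0.70: 0.68
- m = 0.10, c = 0.95: 0.95

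Missed deaths per 300 retrospective survivors are 300 × m × (1 − c), from 1.5 to 18.

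**4. Effect on a null device comparison, discharged survivors.** Assumptions: two cohorts of 500; 40% in-hospital death in every group, leaving 300 survivors each; 15% later mortality; device share rising from 30% to 50% (average 40%, matching the 400 of 1,000 in section 9.3); capture s in all retrospective subjects; no recorded death read as alive.
- s = 0.3: device (90 × 0.15 × 0.3 + 150 × 0.15)/240 = 26.55/240; no device (210 × 0.15 × 0.3 + 150 × 0.15)/360 = 31.95/360; risk ratio 1.25
- s = 0.7: 31.95/240 against 44.55/360; risk ratio 1.08
- s = 0.95: 35.325/240 against 52.425/360; risk ratio 1.01

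With a rise from 35% to 45%, the ratio is 1.12 at s = 0.3 and 1.04 at s = 0.7. Pooled mortality reads 0.15 × (1 + s)/2: 9.8% at s = 0.3 and 12.8% at s = 0.7, against a true 15%.

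**5. The same for overall death, the stated Cox endpoint.** Add the in-hospital deaths, 160 with a device and 240 without.
- s = 0.3: 186.55/400 against 271.95/600; risk ratio 1.03
- s = 0.7: 191.95/400 against 284.55/600; risk ratio 1.01

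With a rise from 35% to 45%, both are about 1.01. These are risk ratios, used as a guide to size; they are not Cox hazard ratios.

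**The case against.** Much of the other side stands.

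- **Retrospective subjects are not all record-only.** A reader might infer that they are. Section 12.1 lets consented pre-approval subjects be followed prospectively, and under even accrual 40% of retrospective 12-month dates fall after approval. This narrows the imbalance without removing it: a patient who consents in person after approval was alive then, so this route adds confirmed survivors while earlier deaths still depend on records.
- **Records may be better than feared.** Section 17 describes the tests as routine care that patients would receive anyway. Outpatient visits near the scheduled times may already be in the charts. Only study-initiated contacts are ruled out.
- **The protocol is silent on cohort handling; it does not declare the cohorts equal.** Strata and censoring rules are often left to a statistical analysis plan, which is not shown. Nothing says that subjects without a recorded death count as alive. Missing censoring wording alone would be no finding. What remains is a schedule that section 12.1 makes impossible for many of the subjects it covers.
- **The larger risk ratios do not describe the planned model.** A reader might infer that a null device effect would appear as 1.08-1.25. That range applies to discharged survivors under assumed 30-70% capture. Overall death includes about 400 in-hospital deaths, which are read from the inpatient chart in both periods.
- **Rising device share is not established.** Section 6.2 speaks of ECMO procedures in Korea, whereas the device group also includes IABP. That devices would look harmful is therefore conjecture.

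**Conclusion.** The point holds in a limited form. The protocol prescribes one contact schedule for all subjects but permits only pre-approval data for retrospective subjects without consent. Ascertainment after discharge therefore differs by cohort, and the Cox analysis of overall death, as written, contains nothing to absorb that difference. The composite is affected as an endpoint, not through any stated Cox model. In-hospital death, the primary endpoint, is not affected.

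The calendar shares rest only on section 11.1 and even accrual. The size of the bias rests on capture and device-share figures that the documents do not give. For overall death the illustrated distortion is small, about 1.01-1.03. For deaths after discharge it runs from about 1.01 at 95% capture to 1.25 at 30%. The change is worth making because it costs little, not because a large bias has been shown.

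**What to change.** - **Sections 12.1 and 12.2:** reconcile them by stating which contacts apply to prospective, consented pre-approval and record-only subjects, and the source of vital status for the last group.
- **Section 15.3, Cox model:** stratify by these three ascertainment groups, giving each its own baseline hazard. A simple split into retrospective and prospective would mix contacted with record-only subjects. Censor record-only subjects at the last documented contact, and no later than approval. Because in-person consent after approval requires survival to that point, treat the pre-approval time of consented subjects under the same rule as record-only time and let them enter the consented stratum at consent.
- **Section 15.3, rates:** show follow-up death and composite rates by cohort beside the pooled figures.

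In-hospital death can stay pooled as far as this point goes.

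**Cost.** The cohort flag follows from the shock and approval dates. Consent status, consent date and last-contact date should be confirmed as captured in the e-CRF. Stratification excludes no patients, but it does not recover missed deaths. Rates from a half-sized cohort have intervals about 40% wider (√2 = 1.41), which is why the pooled figures should stay alongside them.

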## ① Survival and death event investigation

## ② laboratory tests (conducted at 6 months).

|                   |                                                                      |
|-------------------|----------------------------------------------------------------------|
| CBC               | Hemoglobin, WBC, Platelets                                           |
| Chemistry profile | Creatinine, Fasting glucose level, AST,ALT, T-bilirubin, LDH, Sodium |
| Cardiac enzymes   | CPK, CK-MB, Troponin I, NT-proBNP                                    |

**13. Predicted side effects and precautions for use**

In cases of ischemic heart disease, standard percutaneous coronary intervention is performed, and the use of left ventricular assist devices to restore signs of vitality in the event of shock is necessary, so there are no increased side effects resulting from this study. Possible complications during the procedure include systemic embolism, including stroke, coronary artery dissection, perforation, rupture, side branch occlusion, stent migration and damage, and acute thrombosis-induced myocardial infarction and ventricular arrhythmia, but they will not increase due to this study. Stent thrombosis can increase due to early discontinuation of antiplatelet agents such as aspirin and P2Y12 inhibitors taken after the procedure.

**14. Stopping/dropping criteria**

- ① When the subject or legal guardian requests to withdraw from the clinical trial
- ② When the subject refuses to comply with the investigator's instructions or fails to comply with the provisions stated in the consent form
- ③ When the subject's absence makes continuous observation impossible
- ④ When the subject dies for reasons unrelated to the clinical trial
- ⑤ Other cases where the clinical trial coordinator determines that there are problems with the conduct of the clinical trial.

#### Method of handling

- ① If a subject drops out in the middle of the clinical trial, the reason for dropping out and the data related to the clinical trial up to the point of dropping out shall be recorded and stored.
- ② Unless there is a valid reason or justification, those who drop out in the middle shall be included in the safety and efficacy evaluation statistics processing.

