### **15.2. Secondary Endpoints**

- 1) Death in 28 days
- 2) Death during follow-up
- 3) Death, myocardial infarction, stroke, re-admission due to heart failure during follow-up
- 4) Number of days of intensive care unit
- 5) Hospitalization days
- 6) Lactate 24 hour clearance
- 7) Successful removal of left ventricular assist device (IABP, ECMO)

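### Section 14 drops patients who have not withdrawn consent, provides for their data only up to that point and leaves an open exception for excluding them, which can bias the follow-up death analyses

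*Protocol*

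**What the plan says.** Section 14 of the protocol lists five grounds for dropping a subject. The first is withdrawal by the subject or guardian. The others are:

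- ground 2, non-compliance: "When the subject refuses to comply with the investigator's instructions or fails to comply with the provisions stated in the consent form";
- ground 3, absence: "When the subject's absence makes continuous observation impossible";
- ground 4, death for a reason unrelated to the trial;
- ground 5, judgement: "Other cases where the clinical trial coordinator determines that there are problems with the conduct of the clinical trial".

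Two handling rules follow. Under the first, the reason for dropout and "the data related to the clinical trial up to the point of dropping out shall be recorded and stored". The second governs the analysis: "Unless there is a valid reason or justification, those who drop out in the middle shall be included" in the safety and efficacy statistics. The protocol does not say what counts as a valid reason, who decides or when.

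Elsewhere the protocol sets up a way of reaching patients who do not attend. Section 11.1 says that, for a subject who cannot come to the hospital, the responsible person or a delegate "may follow-up and check the subject's survival status and death event by phone". Section 12.2, on the visits at 1, 6 and 12 months, says "Information gathering through phone (landline contact) is also allowed without the subject's visit".

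Section 15.2 lists "Death during follow-up" as a secondary endpoint, together with a composite that contains death. Section 15.3 plans a Cox analysis of overall death.

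**The concern.** The stopping rules fit a trial that assigns a treatment. This study is described as an observational registry, and section 17 says its tests belong to routine care. A patient who ignores instructions, or whose case the coordinator finds problematic, can still die, and that death can still be learned by phone or from the record.

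Two kinds of bias are possible. If such a patient is censored at dropout, the Cox analysis assumes that the later risk equals that of the patients still followed. After cardiogenic shock this is doubtful, because patients who stop cooperating may be deteriorating. That is clinical plausibility; the documents give no data on it. If the patient is instead left out under the exception in the second rule, the analysed group is selected on something that happened after registration, in an open study where the outcome may already be known.

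Ground 4 adds a separate fault. Where the study assigns no treatment, nearly every death can be called unrelated to it. Read literally, an endpoint event then turns the patient into a dropout.

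**Working it through.** **1. The protocol's own dropout figure.** Section 9.3 gives about 88% power for 0.3 versus 0.4 with 400 and 600 patients, and 84% after about 10% dropout. Alpha is not stated; I assume 0.05 two-sided.

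- With k = 1.5 and d = 0.1, the pooled proportion is (0.3 + 1.5 × 0.4)/2.5 = 0.36.
- Inverting the Fleiss continuity correction, n = (n′/4)[1 + √(1 + 2(1 + 1/k)/(n′d))]², gives n′ ≈ 383.5 for n = 400 and n′ ≈ 343.5 for n = 360.
- Power = Φ{[d√n′ − 1.96√(0.36 × 0.64 × (1 + 1/k))]/√(0.21 + 0.24/k)}.
- For 400/600: (1.958 − 1.215)/0.608 = 1.22, power 88.9%. For 360/540: (1.853 − 1.215)/0.608 = 1.05, power 85.3%.

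The stated figures are reproduced to within two points. The 10% enters only as a loss of numbers. The calculation names no endpoint and does not address bias.

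**2. The grounds set against the phone route.**

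| Ground | Consent withdrawn? | Can status still be obtained? |
|---|---|---|
| 1 withdrawal | yes | no |
| 2 non-compliance | not necessarily | often, by phone or record |
| 3 absence | no | consistent with 11.1 and 12.2 only if phone contact has also failed |
| 4 unrelated death | no | the outcome is already known |
| 5 coordinator judgement | no | often, by phone or record |

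The conflict is plain for grounds 2, 4 and 5. For ground 3 it depends on how a site reads the condition about observation being impossible.

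**3. Illustrative size, censoring.** Inputs: 1,000 patients (section 9.3), about 40% mortality (section 15.3), and 10% dropout (section 9.3, assumed here to apply to hospital survivors).

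- Survivors: 1,000 × (1 − 0.40) = 600. Dropped: 600 × 0.10 = 60. Followed: 540.
- Width of the undetermined range: 60/600 = 10 percentage points, whatever the death rate in the 540.
- Example with an assumed 10% mortality among the 540, or 54 deaths: lower bound 54/600 = 9.0%, upper bound (54 + 60)/600 = 19.0%.

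The upper bound needs every dropped patient to die. The range is a worst case and not a forecast.

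**4. Illustrative size, exclusion.** With the same assumed figures, overall mortality is:

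- dropped patients excluded: (400 + 54)/940 = 48.3%;
- dropped patients censored and treated like those followed: 0.40 + 0.60 × 0.10 = 46.0%;
- possible true values: 454/1,000 = 45.4% to 514/1,000 = 51.4%.

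The choice between excluding and censoring alone moves the estimate by 2.3 points, and the second handling rule leaves that choice open.

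**The case against.** Much of the case on the other side is sound.

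- **Absence.** A reader might infer that ground 3 flatly contradicts the phone follow-up. It does not. It applies only when observation has become impossible, and a patient who answers the phone can be observed. The text leaves this to the site, so it needs a clarifying phrase.
- **Data after dropout.** The first rule requires data up to dropout to be kept and does not forbid collecting more. That stands. But it provides for nothing further, and a site following it has no reason to call.
- **Inclusion is the default.** That also stands. The fault is the unlimited exception. An analysis plan could define it, but could not recover deaths that nobody looked for.
- **Primary endpoint.** A reader might infer that in-hospital death is compromised, because the second rule names no endpoint. The documents do not support this as the main effect: in-hospital death is observed during the admission, mostly before these grounds could apply. Even if all 60 survivors in the illustration were removed, the figure would be 400/940 = 42.6% instead of 40%.
- **Size.** The 10% is a general power allowance and not a post-discharge rate under grounds 2, 4 and 5. It may include withdrawals and unreachable patients. Under section 12.1, retrospective subjects without written consent contribute data only until IRB approval, so section 14 hardly touches them. A reader might also compare the 10-point range with the planned difference of 0.3 versus 0.4; that calculation names no endpoint, so the match shows nothing.
- **Consent.** A refusal to comply may amount to refusing further contact. That stands, and the fix must respect it.

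**Conclusion.** The point holds for follow-up death, the composite and the Cox analysis of overall death, and only marginally for in-hospital death. As written, grounds 2 and 5 can end ascertainment in patients who still consent and can be reached. Ground 4 classes an outcome as a dropout, and the second handling rule allows exclusion for a reason that is never defined. Ground 3 needs clarification only.

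The size cannot be fixed from the protocol. If 10% of about 600 survivors were dropped, the follow-up death proportion among survivors would be undetermined over at most 10 percentage points. This rests on carrying the general dropout allowance over to survivors and on making no assumption about those dropped. How much of the range the phone route would recover is unknown, since withdrawals and unreachable patients remain. That censoring would be informative is plausible but not shown in the documents. The amendment is worth making because it is cheap and uses follow-up already planned.

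**What to change.** Amend section 14 as follows.

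1. End data collection only when the subject or representative withdraws consent, and state that refusing further contact or record access counts as withdrawal.
2. Treat grounds 2 and 5 as missed visits. Apply ground 3 only after phone and record checks have failed, and say so.
3. Delete ground 4 as a reason for dropping, and count every death as an outcome.
4. Continue ascertainment at 1, 6 and 12 months, by phone as sections 11.1 and 12.2 already allow or from the record, for all consenting subjects.
5. Replace the second handling rule: analyse all eligible registered subjects with all data collected, censor at last known status, and exclude nobody for a reason arising after registration.

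The cost is amendment wording with IRB approval under section 20.1, and some extra calls by existing staff. No treatment rule changes.
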